### Statistical methods

The adverse event verbatim descriptions will be classified into standardized medical terminology using the Medical Dictionary for Regulatory Activities (MedDRA) version 19.1. AEs will be coded to primary System Organ Class (SOC) and preferred term (PT) using MedDRA. Descriptive statistics will be used to analyse all AEs by causality and relatedness. Changes in vital signs will be described using medians and interquartile ranges. The proportion of screen failures and participants who commenced study drug; proportion who achieve each dose; and, proportion who are retained in the study or revoke consent will be analysed. Secondary outcomes measure: changes in medication tolerability; proportion of participants who reached primary and secondary end points; MA withdrawal and craving severity; and, quality and duration of sleep. These will be tested for statistical significance using Wilcoxon rank-sum test for non-parametric data. All tests of significance will be conducted at a two-sided alpha level of 0.05. As this is an exploratory study we will: (i) conduct analyses of observed data only; (ii) conduct sensitivity analyses which account for missing data by imputation; and, (iii) report missing data and limitations.

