## Materials and methods

### Trial design

This study is an open-label, single-arm, pilot clinical trial of a five-day tapering dose regimen of LDX for acute MA withdrawal. Participants are admitted to an inpatient withdrawal unit for up to seven days (five days of medication and two additional optional days for transition to ongoing treatment [e.g. residential rehabilitation, counselling]) and are followed up via telephone or in person once a week until Day 28 (three weeks post discharge).

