### Sample size

As this is a pilot study, it is not powered to detect differences in treatment efficacy. This study will therefore seek to enrol 15 participants, conventional for studies of this nature [36, 37]. Findings will inform planning for a large-scale RCT of LDX for treatment of MA withdrawal.

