### Data collection

#### Outcomes

*Primary outcomes*. Safety is assessed by Adverse Events (AEs) and vital statistics recorded during each study visit. AEs will be analysed and reported for seriousness, severity, causality, relatedness, and expectedness [41]. Vital signs (heart rate, blood pressure, temperature, oxygen saturation and respiratory rate) are recorded four times daily during the inpatient period. Safety is further assessed through differences in symptoms of psychosis and hostility obtained using the psychosis and hostility items of the Brief Psychiatric Rating Scale (BPRS) [42, 43], and suicidality measured by the Columbia Suicide Severity Rating Scale (C-SSRS) at Days 1 and 5 [44]. Feasibility is measured through the proportion of screen and pre-screen failures and time taken to enrol sample.

*Secondary outcomes*. Medication acceptability is measured by the Treatment Satisfaction Questionnaire for Medications II (TSQM-II) [45], medication adherence (proportion of prescribed doses taken and reasons for missing doses), proportion and type of adjuvant symptomatic medication required, and qualitative interviews. Retention is assessed by the proportion of participants retained in the study until Days 5, 7, 14, 21 and 28. Changes in subjective withdrawal severity are measured at each time point using the Amphetamine Withdrawal Questionnaire (AWQ) [46] through to Day 28. Changes in craving for MA during the inpatient period are assessed using a 100mm Visual Analogue Scale (VAS) [47]. Participant sleep is objectively monitored through continuous actigraphy (Philips Actiwatch 2^®^) and subjective sleep quality is measured with a modified Consensus Sleep Diary (CSD) [48].

To describe the sample additional baseline assessments include: the Wender-Utah rating scale (WURS), to screen for co-existing ADHD [49]; and severity of dependence assessed with the Severity of Dependence Scale (SDS) [50]. Quality of life and level of social support is measured using the Personal Wellbeing Index (PWI) and ENRICHD Social Support Inventory (ESSI), respectively [51, 52].

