## Discussion

To our knowledge this is the first trial of LDX for the treatment of MA withdrawal. Withdrawal is often the first stage of treatment for MAUD. Poorly managed symptoms of withdrawal may be a significant barrier to attaining treatment goals. LDX assisted withdrawal has the potential to improve treatment outcomes through mediating craving [39, 58, 59]. There is currently a paucity of research into treatments for MA withdrawal [10], with multiple sources noting that high quality research is urgently needed [15, 60, 61]. This study follows a novel approach to the management of acute stimulant withdrawal, similar to the management of opioid withdrawal with buprenorphine, which has proven effective in the past [21].

Limitations of this study include the lack of comparison group and small sample size; however, as this is the first time this medication has been used for this indication a single-arm un-blinded pilot study approach is appropriate.

Although not designed to detect efficacy, there are significant strengths to this study. The proposed tapering dose regimen may permit withdrawal symptoms and intensity of craving to be modulated over the acute withdrawal period, potentially assisting people to remain in withdrawal treatment for the duration of their care, providing more time for treatment planning and motivational enhancement. This study proposes a novel approach of commencing with a high dose stimulant more closely aligned with what would be consumed extra-medically by this population. Thus, we aim to reduce the risk of a Type-1 error due to under-dosing. Participants are closely monitored throughout the study period by specialist medical staff which will allow for high resolution safety data. This is further strengthened with a follow-up schedule to three weeks post discharge. The study protocol proposes medication delivery in a closely monitored inpatient withdrawal unit to accurately and safely document AEs, which is important as this medication has not been used in this context previously. Further, the proposed intervention is an add-on to usual care (the participants are not admitted expressly to be enrolled in the trial) increasing generalisability in real-world situations and enhancing relevance in other settings such as residential and outpatient services. Results from this study will provide valuable data for a planned RCT investigating the efficacy of LDX to treat MA withdrawal.

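### The rank-sum test, which compares two independent groups, is assigned to the secondary outcomes of a single-arm trial whose scores are repeated measures on the same 15 people

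*Protocol article*

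**What the plan says.** The Statistical methods section of the protocol article lists four kinds of secondary outcome: change in medication tolerability; the "proportion of participants who reached primary and secondary end points"; severity of withdrawal and craving; and quality and duration of sleep. It continues: "These will be tested for statistical significance using Wilcoxon rank-sum test for non-parametric data". It then adds: "All tests of significance will be conducted at a two-sided alpha level of 0.05".

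The design section reads: "This study is an open-label, single-arm, pilot clinical trial of a five-day tapering dose regimen of LDX for acute MA withdrawal". The Discussion confirms that there is no control: "Limitations of this study include the lack of comparison group and small sample size". The Sample size section states: "This study will therefore seek to enrol 15 participants, conventional for studies of this nature".

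The Outcomes section has the Amphetamine Withdrawal Questionnaire (AWQ) completed at each time point through Day 28 and craving scored on a visual analogue scale during the inpatient stay. The procedure for Days 1–5 adds daily measurement of treatment satisfaction, withdrawal, craving and sleep. No subgroup contrast, historical control or other pair of independent groups is named anywhere.

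**The concern.** The Wilcoxon rank-sum (Mann-Whitney) test takes two independent samples and asks whether one tends to give larger values than the other. In this trial the only quantities available to compare are scores from the same people on different days. Feeding two days' scores into a rank-sum test treats 15 people measured twice as 30 unrelated people. The between-person spread then stays in the error term, although a paired analysis would remove it.

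Two things follow if the text is applied literally. For the repeated scores, the p-value is not calibrated to the stated 0.05, and under the usual positive within-person correlation a real change is more likely to be reported as non-significant. For the proportion reaching end points there is one group and no reference value, so a rank-sum test has nothing to compare.

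The article says that the findings will inform a later randomised trial. A change in withdrawal or craving that is missed for this reason would be a poor input to that planning.

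**Working it through.** **Inputs from the article.** One arm; n = 15; two-sided alpha 0.05; rank-sum test; repeated scores on the same participants. The sample size is set by convention, with no effect size or power behind it, so there is no power figure to reproduce. The figure to check is the nominal 5% level.

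**Assumed inputs.** The article gives neither the within-person correlation (rho) nor the size of change (d, in SD units). Both are shown over a range.

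**Large-sample check of the level.** Take equal variances sigma² at the two time points.

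- Standard error of the mean difference if the samples are treated as independent: sigma × √(2/n).
- True standard error for pairs: sigma × √(2(1 − rho)/n).
- The ratio of the first to the second is 1/√(1 − rho), so the true size of a nominal 5% unpaired test is 2 × [1 − Phi(1.96/√(1 − rho))].

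| rho | 1.96/√(1 − rho) | True size |
|---|---|---|
| −0.3 | 1.72 | 8.6% |
| 0 | 1.96 | 5.0% |
| 0.3 | 2.34 | 1.9% |
| 0.5 | 2.77 | 0.6% |
| 0.7 | 3.58 | 0.03% |

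**Simulation at n = 15.** Bivariate normal before/after scores, exact rank-sum against exact signed-rank, rejecting at p ≤ 0.05, with at least 20,000 replicates per cell. Power cells show rank-sum / signed-rank.

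| rho | Size, rank-sum | Size, signed-rank | Power, d = 0.5 | Power, d = 0.7 | Power, d = 0.8 | Power, d = 1.0 |
|---|---|---|---|---|---|---|
| −0.3 | 7.7% | 4.7% | 27% / 19% | 43% / 33% | 52% / 41% | 69% / 58% |
| 0 | 4.3% | 4.7% | 24% / 24% | 42% / 41% | 52% / 50% | 71% / 70% |
| 0.3 | 1.8% | 4.7% | 21% / 32% | 42% / 55% | 53% / 66% | 74% / 84% |
| 0.5 | 0.8% | 4.8% | 18% / 42% | 40% / 69% | 54% / 80% | 78% / 94% |
| 0.7 | 0.1% | 4.8% | 14% / 61% | 39% / 88% | 56% / 95% | 82% / 99% |

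Repeat runs of the same cells differ by one or two percentage points. With only 10 complete pairs the pattern is the same: rank-sum size is 2.0%, 0.8% and 0.2% at rho 0.3, 0.5 and 0.7.

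The signed-rank test holds its level at every correlation tried. The rank-sum test is close to 5% only near rho = 0. Raising rho from 0.3 to 0.7 leaves rank-sum power at d = 0.7 almost unchanged, while signed-rank power rises from about 55% to 88%. That difference is the information lost by ignoring the pairing.

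**The proportion.** No arithmetic applies. There is one group of 15 and no comparator or target value, so the quantity can be estimated but not tested with a rank-sum test.

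**The case against.** The strongest reply is that little depends on these tests. The primary outcomes are safety and feasibility, and the article analyses them with descriptive statistics, medians with interquartile ranges, and proportions. Every secondary objective is worded as description. The article says of the study that "it is not powered to detect differences in treatment efficacy" and calls it exploratory, and no decision rule uses a secondary p-value. Without a control group, even a correct paired p-value could not separate a drug effect from the natural course of withdrawal, which the Introduction puts at about 7–10 days. All of this stands, and it limits the severity.

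It can also be said that the wording is probably a slip for signed-rank, and that an analysis plan not shown here may have it right. That is plausible. It does not remove the point, because the article positively names a test that does not fit its design.

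Four stronger readings are tempting and are not supported.

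- **That the error inflates false-positive findings.** With positive correlation it does the opposite. Inflation appears only if correlation is negative.
- **That strong conservatism is certain.** It depends on a correlation that the article does not give. At zero correlation the two tests perform alike, and for large changes the power gap narrows (78% against 94% at 1.0 SD and rho 0.5).
- **That change in treatment satisfaction cannot be tested because there is no pre-treatment value.** Satisfaction is recorded daily on Days 1–5, so a paired between-day change is available.
- **That a meaningless test of retention is sure to be run.** The section deals separately with the proportion retained and names no test there, and its qualifier about non-parametric data can be read as limiting the test to scores. The proportion reaching end points is nevertheless in the list to which the testing sentence refers, so the wording needs correcting.

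**Conclusion.** The point holds as a should-fix. The named test is wrong for a single-arm trial with repeated measures, and nothing in the article supplies the two independent groups that it needs. Its consequence is confined to the secondary outcomes; the primary safety and feasibility results are untouched.

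At n = 15 and an assumed within-person correlation of 0.3 to 0.7, the true size is about 2% down to 0.1% instead of 5%, and power at 0.7 SD is about 40% where a paired test would have about 55% to 88%. These figures assume normal scores with equal variance at the two time points. The direction of the error rests on positive correlation, which is what one expects of scores from the same person but is not documented in the article. The mismatch between test and design does not depend on any of these assumptions.

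**What to change.** In Statistical methods:

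1. Replace the rank-sum test with the Wilcoxon signed-rank test on prespecified pairs of time points (for example baseline or Day 1 to Day 5, as the assessment schedule in Fig 1 allows). Report the paired median change with its 95% CI.
2. Take the proportions reaching end points out of the testing sentence. Report them as n/N with exact 95% CIs and no test.
3. If change in treatment satisfaction is tested, state that it is a paired comparison between named treatment days.

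A repeated-measures model for the daily withdrawal and craving series is optional. It is not needed to correct the error, and it brings distributional and trend assumptions that are hard to check with 15 people. Dropping significance tests for the secondary outcomes and reporting estimates with intervals would also be coherent with the descriptive objectives.

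The cost is one or two sentences of wording. No new data, visits or participants are needed.

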LDX doses of up to 250mg per day have been found to be safe and tolerable in both stimulant-naïve people and a pilot study of people who use MA [23, 28, 29]. A tapering dose regimen is proposed in this protocol to allow for maximum potential attenuation of early withdrawal by providing reducing stimulant exposure through the first five days, when withdrawal symptoms are at their most severe and ensure no residual withdrawal from LDX upon ceasing treatment due to the tapering dose. As the ineffective treatment of MA withdrawal symptoms may lead to higher rates of relapse to use [30, 31], the ability for LDX as a prodrug of dexamphetamine to ameliorate withdrawal symptoms and craving for MA has the potential to improve treatment outcomes during acute withdrawal [32].

This report is a protocol for an open-label, single-arm pilot clinical trial. The protocol was developed in conjunction with SPIRIT guidelines and adheres to the Australian National Statement on Ethical Conduct in Human Research, and Good Clinical Practice guidelines [33–35].

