### Objectives

This study aims to assess a five-day tapering-dose regimen of LDX for the management of acute MA withdrawal in an inpatient withdrawal setting. We hypothesise that a tapering dose of LDX will be safe and feasible to deliver during inpatient withdrawal from MA.

The primary objective is to determine the safety and feasibility of a 250mg tapering dose of LDX over five days of inpatient treatment. Secondary objectives are: (i) to describe the acceptability of the treatment regimen to participants; (ii) to describe participant retention to the protocol; (iii) to describe changes in withdrawal severity, and (iv) MA craving during and after the treatment regimen; and (v) to describe the sleep wake cycle of people with acute MA withdrawal receiving a five-day tapering dose of LDX.

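### Change in withdrawal severity and craving is tested as an unpaired comparison of observed scores, which may overstate improvement if the more symptomatic participants are lost

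*Protocol article*

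**What the plan says.** All references are to the protocol article.

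- **Objectives.** Two of the secondary objectives are "iii) to describe changes in withdrawal severity, and (iv) MA craving during and after the treatment regimen".
- **Outcomes.** AWQ is collected at each time point to Day 28. For craving, "Changes in craving for MA during the inpatient period are assessed using a 100mm Visual Analogue Scale (VAS"). The Procedure section has both rated daily on Days 1 to 5.
- **Statistical methods, missing data.** "As this is an exploratory study we will: (i) conduct analyses of observed data only; (ii) conduct sensitivity analyses which account for missing data by" a method it names as imputation. The third commitment in that sentence is to "report missing data and limitations". Since imputation is labelled a sensitivity analysis, the observed-data analysis is the lead one.
- **Statistical methods, test.** The secondary measures, including withdrawal and craving severity, are to be tested with the Wilcoxon rank-sum test at two-sided 0.05. No paired test or repeated-measures method is named.
- **Possible links between symptoms and loss.** The Introduction reasons: "As the ineffective treatment of MA withdrawal symptoms may lead to higher rates of relapse to use". The Discussion describes the taper as "potentially assisting people to remain in withdrawal treatment for the duration of their care". Under Study withdrawal criteria, needing more than 40 mg of diazepam in 24 hours for symptoms counts as an adverse event. Such an event leads to withdrawal from the trial if it is judged potentially treatment related and a risk to safety.
- **Continued assessment.** Under Participant study discontinuation, people who stop treatment are offered all remaining assessments. Data collection ends when consent is revoked.

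**The concern.** There is one arm, so the groups that a rank-sum test of change can compare are time points. The test ignores that the later scores come from a subset of the same people. If those who leave were more symptomatic than those who stay, the later group is milder by selection, and part of the apparent fall in AWQ or VAS is a change in who is being rated.

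Craving is most exposed: a person who leaves the unit on Day 3 has no later inpatient rating, whatever their willingness to continue in the study.

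No control arm shares the distortion. The Sample size and Discussion sections say the findings will inform a larger randomised trial, so an inflated description of change could colour its planning.

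**Working it through.** **Inputs from the protocol.** 15 participants, set by convention; observed data first; rank-sum test; two-sided 0.05. No dropout rate, SD, correlation or expected change is given, so there is no figure to reproduce. Everything below on loss and score behaviour is assumed.

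**Step 1: where the bias enters.** Let S be the participants still rated on Day 5, and p the fraction lost. Then

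mean of S on Day 5 − mean of all on Day 1 = (mean change within S) + (Day 1 mean of S − Day 1 mean of all).

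The last bracket is pure case mix and equals −p × (Day 1 mean of leavers − Day 1 mean of stayers). For illustration, if 3 of 15 leave (p = 0.20) and leavers start 0.5 SD higher, it is −0.20 × 0.5 = −0.10 SD with nobody improving. A paired analysis removes this term.

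**Step 2: loss driven by the latest recorded score.** Simulated model: 15 participants; daily scores on Days 1 to 5 with SD 1 on Day 1; random-intercept share 0.6; random slope SD 0.5; true change −0.5 SD; chance of leaving after each of Days 1 to 4 dependent on that day's score, with odds ratio 2 to 3 per SD.

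| Loss by Day 5 | Number lost | Overstatement, unpaired (SD) | Divided by 0.5 |
|---|---|---|---|
| 13% | 2 of 15 | 0.06 to 0.09 | 12% to 18% |
| 20% | 3 of 15 | 0.10 to 0.14 | 20% to 28% |
| 33% | 5 of 15 | 0.16 to 0.23 | 32% to 46% |
| 40% | 6 of 15 | 0.21 to 0.29 | 42% to 58% |

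At an odds ratio of 1.5 the overstatement was 0.04 to 0.13 SD. With zero true change, the same 0.06 to 0.29 SD appears as improvement.

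In the same model the paired difference among those with both ratings was biased by at most 0.03 SD. A random-intercept mixed model on all ratings was off by about 0.01 to 0.04 SD: at 20% to 40% loss it gave −0.50 to −0.53, against −0.49 to −0.51 with full data and −0.60 to −0.77 unpaired. The distortion therefore comes from the unpaired comparison; using observed data is not by itself the cause.

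**Step 3: other loss mechanisms.** Second model: 15 participants, no true change, baseline-to-later correlation 0.3 or 0.6, odds of loss tripled per SD. Bias in SD; negative means apparent improvement.

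| Loss depends on | Comparison | 10% lost | 20% | 33% | 50% |
|---|---|---|---|---|---|
| Nothing (random) | both | 0.00 | 0.00 | 0.00 | 0.00 |
| Baseline score | unpaired | −0.03 to −0.06 | −0.06 to −0.11 | −0.09 to −0.18 | −0.13 to −0.26 |
| Baseline score | paired | +0.04 to +0.07 | +0.07 to +0.13 | +0.12 to +0.21 | +0.18 to +0.31 |
| Later, unrecorded score | unpaired | −0.10 | −0.18 to −0.19 | −0.29 to −0.30 | −0.44 |
| Later, unrecorded score | paired | −0.04 to −0.07 | −0.07 to −0.13 | −0.12 to −0.21 | −0.18 to −0.31 |

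Unpaired, both severity-related mechanisms lean towards improvement. Paired, the sign depends on the mechanism, and loss driven by a score never recorded still leaves bias. The near-absence of paired bias in Step 2 is thus specific to that model.

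**Step 4: the test.** With loss driven by the later score and no true change, the rank-sum test rejected in 0.9% to 4.4% of trials at 10% to 20% loss, 4.7% to 7.0% at 33% and 8.8% to 10.7% at 50%. With random loss it rejected in 0.5% to 3.0%, because it ignores the correlation between a person's own scores; the signed-rank test gave 3.5% to 4.9%. At low loss the estimate is the greater worry, not the p-value.

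**Step 5: scale.** With 15 ratings on Day 1, 12 on Day 5 and SD 1, the standard error of the unpaired difference is √(1/15 + 1/12) = 0.39 at zero correlation and √(1/15 + 1/12 − 2 × 0.6/15) = 0.26 at correlation 0.6. The bias at 20% loss (0.10 to 0.14) is well below either.

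**The case against.** The strongest reply is that observed-data analysis is not the fault: a paired observed-data change did about as well as a mixed model in Step 2, and a mixed model is itself fitted to observed ratings. That stands, and it is why the point is put as one about the unpaired comparison. The named test may be a slip for the signed-rank test; if so, correcting it removes most of the problem.

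Much is also already in place: the plan promises to "conduct sensitivity analyses which account for missing data by imputation", to report missing data, and to present retention at Days 5, 7, 14, 21 and 28. For AWQ, stopping treatment does not by itself end ratings. These commitments reduce the concern. They do not change the lead comparison, and the offer of continued assessment cannot supply inpatient craving scores after someone has left. The imputation method may be set out in a fuller document and its absence here is not at issue.

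Finally, change in a single arm is not a treatment effect under any missing-data method: the Introduction says acute withdrawal lasts around 7 to 10 days, and the Discussion concedes the lack of a comparison group. The protocol does not say that AWQ or VAS change will set the later trial's effect size. This stands and limits the consequence.

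A reader might infer that the protocol expects symptom-driven dropout. It does not say so: the Introduction concerns relapse, not missed ratings, both it and the Discussion speak only of possibilities, and no dropout rate is stated. A reader might also infer that the bias always favours the drug. Under random loss there is none, and paired change can be biased the other way.

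**Conclusion.** The point holds in limited form. As written, the lead analysis of AWQ and VAS compares time points as if they were independent groups, and it may overstate improvement if loss is related to severity. The size is about 0.06 to 0.29 SD, conditional on assumed loss of 13% to 40% and assumed odds ratios of 2 to 3 per SD of current score. It is strongest for craving and lessened for AWQ. Severity is minor: the outcomes are secondary and descriptive, the pilot is not powered for efficacy, and safety and feasibility are primary.

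**What to change.** In Statistical methods:

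1. Base the main estimate of change in AWQ and VAS on within-participant change, from a repeated-measures mixed model with a participant random intercept and study day as a category, fitted to all ratings from everyone who received study drug. Early leavers then contribute their ratings up to departure.
2. Report the paired change with a Wilcoxon signed-rank test beside it, in place of the rank-sum test.
3. Show Day 1 scores separately for participants with and without a Day 5 rating.
4. Let at least one of the already planned imputation analyses assume no improvement in those lost. The mixed model relies on loss depending on recorded scores, and this analysis covers departure from that.

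The cost is a few lines of text and a little programming, with no new data, visits or participants. The estimated improvement may be smaller or less precise, and with 15 participants only a simple covariance structure can be fitted.
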